#### Staff

CIIC centers will have 2 auxiliary nurses, 2 nurse assistants, and 30 caregiving volunteers. Auxiliary nurses in Thailand have a bachelor’s degree in public health, underwent an internship at primary health care centers, and received accredited advanced training in caregiving that certifies that they have achieved minimum professional standards and technical quality. Volunteers who received caregiving training will assist the auxiliary nurses.

#### Applicants

The CIIC temporary respite care service will be provided to applicants with full-time, unpaid family caregivers caring for dependent individuals who are ≥60 years old and meet the eligibility as assessed using the ADL and CBI, as described in the following sections.

### ADL Criteria

In order to be eligible to be admitted to the CIIC facility, the family caregiver must be personally providing the care recipient with assistance for at least 2 of the following 6 ADL. The first is bathing: The family caregiver is assisting the older adult with bathing, including help with washing, shampooing, getting in or out of the tub or shower, brushing teeth, and other aspects of personal grooming (Bathing ADL score 0). The second is dressing: The family caregiver is assisting the older adult with dressing, including helping the individual put on or take off clothing and footwear (Dressing ADL score 0 or 1). The third is toileting: The family caregiver is helping the older adult get on or off the toilet, commode, or bedpan as well as clean themselves, or the individual is incontinent (Toileting ADL score 0 or 1). The fourth is transferring: The family caregiver is helping the older adult get to and from a bed or chair (Transfer ADL score 0 or 1). The fifth ADL is walking or mobility: The family caregiver is helping the older adult move from one stationary point to another by removing obstacles, opening doors, and assisting with canes, wheelchairs, or other assistive devices (Mobility ADL score 0 or 1). The sixth is eating or feeding: The family caregiver is helping the older adult who has difficulty chewing or swallowing without assistance or needs partial or total help with eating (Feeding ADL 0 or 1).

### CBI Criteria

On the assessment of caregiver burden, the following 2 eligibility criteria are required to utilize the respite care service: time dependency items score >17 and physical health items score >14.

If there is only one person in the family acting as a caregiver for the older adult with the qualifying ADL criteria and the caregiver has to leave the house to travel, the older adult would qualify for admission to the CIIC based on the available capacity of the facility on the appointment days.

These criteria can be revised by stakeholders depending on the estimates of the population to be served, budget of the municipality, and capacity of the facility.

### Resources

To accommodate short-term stays, the CIIC intervention requires buildings and care facilities. Researchers have discussed this with the administrative officers of the study site subdistrict and obtained commitments to let the CIIC center use public buildings and infrastructure with beds, bathrooms, kitchens, washrooms, air conditioners, televisions, refrigerators, and outdoor facilities such as gardens, walkways, and sports facilities for the 24/7 care of 5-10 older adults.

The CIIC facility will employ dedicated full-time auxiliary nurses and other staff for this research. The CIIC service will not be delivered by existing primary health care nurses. Therefore, the busy routine of the primary health care facility will not affect the CIIC service or be disrupted. Access to health care in case of medical care needs of the participants will be secured by establishing a link between the CIIC and primary health care center before starting the study. In addition, for smooth linkage, the researcher will link to local health facilities that will be coordinated by the local municipal authority before starting the study.

The existing universal health coverage scheme covers health services 100% free of charge. The primary health care services are accessible by any Thai citizen. There is a referral system to the secondary district hospital, and an ambulance service is also available 24 hours a day.

### Outcome Measurements

Validated instruments commonly used in aging and LTC research were carefully selected in order to objectively assess the impact of the CIIC intervention. Most of the instruments exist in the Thai language and have been validated in previous studies and programs in Thailand. In addition, the research team will conduct pilot testing of the instruments for the target population and ensure the reliability of all the instruments in the study setting and context.

#### Primary Outcome

The primary outcome is the burden of family caregivers measured at a 6-month follow-up appointment. The CBI [14,15] will be applied to measure the family caregiver’s burden at baseline (month 0) and then again at month 6. CBI is an internationally well-validated measurement tool with a 24-item, 5-point Likert scale with the following 5 dimensions: time dependence burden (5 items), developmental burden (5 items), physical burden (4 items), social burden (5 items), and emotional burden (5 items).

The total scores will be summed, with total scores >36 indicating a risk of “burning out” whereas total scores >24 are considered indicative of “a necessity to seek some form of respite care.”

#### Secondary Outcomes

Secondary outcomes consist of biopsychosocial indicators including ADL, depression, and QOL of older people, which will be compared between intervention and control groups.

Functional ability will be assessed by applying the Barthel Index for ADL assessment [16], which measures the level of ability for 10 basic items (bowel movement, incontinence, grooming, toileting, feeding, transfer, mobility, dressing, stairs, bathing). Total possible scores range from 0 to 20, with lower scores indicating increased disability.

Depression will be screened by applying the Geriatric Depression Scale (GDS), which is internationally commonly used, validated, and regularly used in Thailand [17].

Health-related QOL will be measured with the EQ-5D-5L questionnaire [18] using the EQ visual analogue scale (EQ VAS) [18,19]. A validated Thai version of the instrument is already available and will be used after piloting. The EQ-5D-5L measures 5 dimensions with 5 levels: mobility, self-care, usual activities, pain/discomfort, and anxiety. The EQ VAS is a measure of overall self-rated health status with a vertical VAS where the end points are labeled “Best imaginable health state” and “Worst imaginable health state.”

Cost for the intervention will be calculated in terms of intervention cost, family cost, and community cost. The details of the intervention cost will inform the estimated cost when expanding the area covered by the CIIC services.

The first possible outcome of the implementation of the CIIC intervention is promoting the capacity of the family caregivers through technical training, early detection of dependency problems, and respite care when the caregiver is overburdened in addition to linking families and primary health care services. The intervention components such as the (1) community respite home and (2) technical capacity building of the caregiver are directly targeting the reduction of caregiver burden.

Therefore, we set caregiver burden as the primary outcome of the study. ADL is also an important outcome of the component. Although we set these as the primary and secondary outcomes, respectively, in terms of the research methodology, they are both important outcomes of the study.

Selecting an outcome that is directly related to most of the intervention practically, we chose caregiver burden as the primary outcome. In a country with an FLTC system as its backbone, this outcome is more practical.

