**Methods:**

This paper describes a cluster randomized controlled trial comprised of 6 intervention clusters and 6 control clusters that aim to recruit 2000 participants in each arm. This research protocol has been approved by the World Health Organization Ethics Review Committee. The intervention clusters will receive an integrated model of care structured around (1) a community respite service, (2) the strengthening of family care capacity, and (3) an exercise program that aims to prevent entry into long-term care for older people. Control group clusters receive usual care (ie, the current system of long-term care common to all provinces in Thailand), consisting principally of a volunteer-assisted home care service. The trial will be conducted over a period of 2 years. The primary outcome is family caregiver burden measured at a 6-month follow-up, as measured by the Caregiver Burden Inventory. Secondary outcomes consist of biopsychosocial indicators including functional ability, as measured using an activity of daily living scale; depression, as measured by the Geriatric Depression Scale; and quality of life of older people, as measured by the EuroQol 5-dimensions 5-levels scale. Intention-to-treat analysis will be followed.

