### Inclusion Criteria for Study Participants

The inclusion criteria are >60 years of age, has a family caregiver(s), either male or female, and resident in study site districts.

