#### Registration

All the families assessed to be eligible for respite care services will be invited to register for the CIIC center’s temporary respite care services, which is not part of the primary health care center of the subdistrict. The services will be provided by newly established CIIC centers staffed with professional staff and volunteers who will provide assistance to family caregivers whenever they find it challenging to sustain caregiving of an older family member. The maximum length of stay is 10 days during the 6-month intervention. Our previous survey study found that 6.5% of older persons had decreased capabilities for ADL that required caregiver assistance [11]. Therefore, the estimated number of persons needing respite care is 130 people in a year; 50% (65/130) may be without a caregiver. These individuals will be provided with residential care; therefore, our calculations show that 5 beds would be sufficient for 10 persons at 2 weeks per year. This might not be enough beds during certain periods of the year. Therefore, a booking service will be provided.

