### Statistical Methods

The analysis will follow the intention-to-treat analysis approach. Outcomes will be compared between intervention and control clusters after 6 months of intervention.

To assess the effectiveness of the intervention, the primary outcome, CBI, will be compared between intervention and control arms after 6 months of intervention. Depending on the nature of the variables, *t* tests, chi-square tests of cluster summary measures, or multivariate analyses will be applied. Data distribution and homogeneity will be checked and ensure the assumption of statistical tests. Cluster-level summary statistics will be compared. A random effects model will be applied to control possible confounders in individual and cluster levels.

The intervention in the CIIC trial is a complex intervention with several components of prevention, training, and service. It is basically empowerment of the community. Therefore, a village as a random effect is due to population and social economic status, and participation of the community is considered as source of variation.

To evaluate the impact of the intervention on the secondary outcomes (ADL for dependency, GDS for depression, and EQ-5D-5L for QOL), the analyses will compare the 2 arms by applying a multivariate analysis of variance model.

Afterwards, the cost of the intervention will be analyzed in terms of both the primary outcome and secondary outcomes. Statistical significance is defined as *P*<.05 with 95% confidence intervals.

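### The stated ADL analysis makes no use of baseline ADL and has no analysis of new dependency, so any prevention effect of the exercise programme is diluted in a whole-sample Barthel mean

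*Protocol article*

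**What the plan says.** **Aim.** The abstract describes "an exercise program that aims to prevent entry into long-term care for older people". The Care Prevention Exercise Program section offers it to all older adults in the intervention clusters, and Table 1 gives preserving function and preventing long-term care need as its purpose in households with active or less dependent older adults.

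**Who enters.** "The inclusion criteria are >60 years of age, has a family caregiver(s), either male or female, and resident in study site districts". There is no dependency criterion.

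**Expected dependency.** The Registration section, under the respite service, cites an earlier survey in which "6.5% of older persons had decreased capabilities for ADL that required caregiver assistance", and concludes that "the estimated number of persons needing respite care is 130 people in a year".

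**Outcome and analysis.** Secondary Outcomes names the Barthel Index as the measure of functional ability: "Total possible scores range from 0 to 20, with lower scores indicating increased disability". Of caregiver burden and ADL the same section says that "they are both important outcomes of the study". Statistical Methods says "Outcomes will be compared between intervention and control clusters after 6 months of intervention" and, for ADL, depression and quality of life together, that "the analyses will compare the 2 arms by applying a multivariate analysis of variance model". It does not say that baseline ADL enters this model, and it names no analysis of new dependency or of decline among people independent at entry. ADL is nevertheless collected at baseline and again at 6 months (Screening and Assessment of Family Burden and LTC Capacity; Data Collection and Follow-Up).

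**The concern.** People who need no ADL help at entry are likely to be near the top of the Barthel scale. They can hardly improve, so a preventive benefit in them shows only as fewer declines. The scale can register a decline. The difficulty is that few declines are likely in 6 months, and the stated analysis averages them over everyone. The spread of that average comes largely from people who were already dependent, whose differences in score at entry carry no information about prevention.

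At stake is how a null result is read. Principal Findings presents the exercise programme as having the potential to prevent dependency. An unadjusted comparison that misses even a halving of new dependency could be reported as no effect on functional ability.

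**Working it through.** **The plan's own figure.** 0.065 x 2000 = 130, which matches the Registration section: the 6.5% is applied to one arm of 2000. The complement is 1870 of 2000, or 93.5%.

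**Inputs from the protocol.** 2000 per arm; up to 20% loss, so 2000 x 0.8 = 1600 analysed; 6.5% dependent; Barthel 0-20; alpha 0.05 (taken as two-sided).

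**Assumed, not in the protocol.** Dependent people are spread evenly over Barthel 2-16 (mean 9, SD 4.32). The others score 19 or 20 (mean 19.5, variance 0.25). New dependency over 6 months in control is 1%, 2% or 4%; each case loses 5 points; the programme halves incidence. Clustering is ignored at first.

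**Where the variance lies.**
- Overall mean: 0.065 x 9 + 0.935 x 19.5 = 18.82.
- Dependent group's share: 0.065 x (4.32² + (9 - 18.82)²) = 7.48.
- Everyone else's share: 0.935 x (0.25 + (19.5 - 18.82)²) = 0.67.
- Total 8.15, SD 2.85. About 92% of the variance (7.48/8.15) is due to the 6.5%.

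**Unadjusted mean at month 6.** Difference = 0.935 x (incidence/2) x 5. SD = square root of (8.15 + 0.935 x incidence x 25). SE = SD x square root of (2/1600).

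| Control incidence | Difference | SE | Difference/SE | Power |
|---|---|---|---|---|
| 1% | 0.023 | 0.102 | 0.23 | 6% |
| 2% | 0.047 | 0.104 | 0.45 | 7% |
| 4% | 0.094 | 0.107 | 0.88 | 14% |

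Simulation under the same assumptions gives 5%, 8% and 13%.

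**New dependency among those independent at entry.** 1600 x 0.935 = 1496 at risk per arm, so about 15, 30 or 60 control events against 7.5, 15 or 30. The ratio (pc - pt) / square root of {[pc(1 - pc) + pt(1 - pt)]/1496} is 1.59, 2.25 and 3.21, giving power of 35%, 61% and 89%. Simulation gives 35%, 64% and 90%. This assumes that dependency status is recorded without error.

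**Mean Barthel adjusted for baseline Barthel (simulation).** 35%, 64% and 90% with no measurement noise; 18%, 39% and 79% with noise of SD 2 at month 6 in dependent people; about 13%, 29% and 68% in a further run with added measurement noise.

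**Smaller effect.** With a 30% reduction, the unadjusted mean has 5-8% power and the new-dependency comparison 14-43%.

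**Other assumptions.** Apply the protocol's design effect: 1600/1.2 = 1333 effective per arm. Let the dependent group average 10-14, the others 19.5-20, and the drop be 4-8 points. The unadjusted mean then has 4-14% power at 1-2% incidence (counting only rejections in the programme's favour, hence values below 5%) and 13-48% at 5%. New dependency has 30-54% at 1-2% and 91% at 5%.

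**Clustering.** A design effect of 1.2 with about 333 per village implies an intracluster correlation of 0.2/(333 - 1) = 0.0006; anything larger lowers every figure. Even with no variation between villages, testing on 6 against 6 village summaries brings the new-dependency power at 1-2% incidence down to about 30-55%.

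**The case against.** The strongest reply is that the outcome is not at fault. Under the same assumptions the Barthel mean, once adjusted for its baseline value, has as much power as the new-dependency comparison when there is no noise. Most of the loss therefore comes from ignoring baseline. This stands, and it is why the Barthel should be kept.

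A second reply is that covariates are commonly left to an analysis plan, which is not shown. Statistical Methods also mentions a random effects model for individual and cluster confounders, and the screening section calls the first assessment a baseline for measuring impact. This stands in part. The random effects sentence is not tied to ADL, whereas the sentence on the secondary outcomes names its own model and mentions no baseline. If an analysis plan already adjusts ADL for baseline, that half of the point is answered.

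Third, the 6.5% is a survey figure used for bed planning. A reader might infer that 93.5% of this trial's participants start without ADL needs. The documents do not show that: requiring a family caregiver may raise the dependent share, and needing no caregiver help does not prove a score of 19 or 20, since the Barthel also covers stairs, continence and grooming.

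Fourth, the Objectives section lists impact on ADL, not prevention of dependency, and caregiver training is directed at households with dependent older adults. Their Barthel scores are a legitimate target. This stands, and supports reporting them separately.

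**Conclusion.** The point holds in a limited form. As written, the ADL comparison dilutes a prevention effect: about 5-13% power under the assumptions stated, against 35-90% for new dependency among those independent at entry and 13-90% for a baseline-adjusted mean. The incidence, the size of the drop and the baseline scores are all assumed, the 6.5% is only a guide to this sample, and village clustering lowers every figure.

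Two stronger readings are tempting and not supported. One is that the Barthel is nearly blind to prevention; baseline adjustment recovers much of the power on the same scale. The other is that a null result is almost certain; the unadjusted comparison reaches 13-48% power if 6-month incidence is near 5%. Nor does the protocol say that mean Barthel alone will decide whether dependency was prevented.

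ADL is a secondary outcome and the primary outcome, caregiver burden, is untouched. The change is still worth making because ADL is called important, the baseline data exist, and the stated method leaves them unused.

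**What to change.** 1. Keep the Barthel Index as the ADL secondary outcome, but analyse month-6 Barthel adjusted for baseline Barthel, with village as a random effect.
2. Add a prespecified secondary analysis of new ADL dependency at 6 months among those independent at baseline, with village accounted for. Define it from the Barthel items already collected. The two-of-six ADL rule in the ADL Criteria section should not simply be borrowed: it governs respite admission, depends on the caregiver personally giving the help, and the CBI Criteria section lets stakeholders revise the admission criteria.
3. Report Barthel results separately for those dependent at entry.
4. State that a null mean-Barthel result does not rule out a preventive effect, and that the 6-month data do not measure entry into long-term care or hospitalization.

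Cost: changes to the analysis text and one added outcome definition, with no new data. The downside is one extra analysis with few events (about 15-60 in the control arm under the assumed incidences), so its estimate will be imprecise.

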### Sample Size

A sample of 4000 community-residing older adults will be recruited, with 2000 adults in each arm of the study (control and intervention), which our calculations show should suffice for the power required by the study. Including 1500 participants in each arm should be ample to detect the effect size difference of 0.5 unit with an SD of 4 between the 2 arms. STATA version 11SE (Stata Corporation, College Station, TX) was utilized for sample and power estimations. The precision levels applied are a *P* value of .05 with a 95% confidence interval. The sample size is inflated (1) for a design effect of 1.2 for applying a cluster randomized design and (2) to compensate for potential nonresponses and drop-outs of up to 20% during recruitment and the study. After inflation, a total sample size of 4000 is estimated to be required for the study. Moreover, the sample size will be sufficient for the estimation of key parameters such as mean CBI, ADL, and health-related QOL indicators in the study population.

There will be 6 clusters in each arm. The cluster size is in the range of 300-350. Within each cluster, individual participants meeting eligibility criteria will be recruited consecutively. Informed consent will be requested from a representative of each cluster before randomization and from each older participant and a family caregiver after randomization.

### Randomization

#### Sequence Generation

Cluster randomization will be used to prevent contamination between the intervention subdistrict and control subdistrict [20]. It is not possible to randomize the villages from different administrative areas or municipalities and directly assign them to an intervention and control arm. Internal randomization will be practiced to randomly recruit 6 eligible clusters within the intervention arm municipality, which has 10-15 villages; likewise, the same will be done in the control arm [20].

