## Methods

### Trial Design

This is a 2-arm, parallel-design, interventional study designed as a cluster randomized controlled trial. A total of 4000 participants will be recruited in 12 clusters, 6 in the intervention group with 2000 older adults and 6 in the control group with 2000 older adults in Chiang Mai province, Thailand.

The unit of randomization, cluster, is a village. Participants in intervention clusters will receive the CIIC intervention after screening for eligibility. The eligibility criterion for a cluster is a village that has more than 300 older persons over 60 years of age at the time of randomization.

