### Study Setting

Chiang Mai, Northern Thailand is the location of the study. There are 284,457 older adults in Chiang Mai city according to the 2019 provincial report. Older adults account for 18% of the population, which is higher than the national proportion of people ≥60 years old (16%). Chiang Mai is culturally similar to many neighboring ASEAN countries in terms of caring for older parents as a family tradition and social value.

Two subdistricts involved in the study, sub-district XXX (10 villages) for intervention and subdistrict YYY (15 villages) for control, are in the same Muang Chiang Mai district of Chiang Mai province. They are geographically distant from each other. They have similar demographic and sociocultural characteristics. Both subdistricts have a similarly sized population (>18,000 people), with similar aging rates (>18% of the population is >60 years old), according to local population statistics. People in both subdistricts are mostly Thai people who have access to health care services through the national health insurance system and social welfare services for older people covered by municipality funds.

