#### Random Allocation

A random number will be generated to recruit villages randomly within each arm. A statistician blinded to the study will generate random numbers for each arm of the study. Control arm and intervention arm villages are geographically distant and administratively exclusive, yet they are in the same province and similar demographically, socially, and culturally to evaluate social interventions.

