#### Challenges and Limitations

Cluster randomization may increase the risk of imbalance in the 2 arms at baseline. This approach of randomization we practiced in CIIC may have limitations but would minimize the residual confounders caused by differences in characteristics of the municipalities. However, this is the best pragmatic approach for the current trial. The results of randomization should be checked carefully at baseline by comparing the aggregate-level summary.

We do not have data about the desirability of temporary, short residential stays at the CIIC facility for older adults and their families. We may have underestimated the demand and therefore, also the required resources. Researchers have consulted with local governments about the possibility of tapping into reserve capacity and resources. Social distancing measures in the COVID-19 pandemic delayed the activities, but we adhered to those measures to ensure the safety of participants.

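### The study is called cluster randomized, but villages are only randomly selected within two subdistricts that each hold one arm, so treatment is fully confounded with subdistrict

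*Protocol article*

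**What the plan says.** Trial Design in the protocol article gives the label: "This is a 2-arm, parallel-design, interventional study designed as a cluster randomized controlled trial". It adds: "The unit of randomization, cluster, is a village".

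Three other sections describe something different.

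- Study Setting names the two areas with their roles: "sub-district XXX (10 villages) for intervention and subdistrict YYY (15 villages) for control".
- Sequence Generation rules out allocating villages to arms across areas: "It is not possible to randomize the villages from different administrative areas or municipalities and directly assign them to an intervention and control arm". In its place, "Internal randomization will be practiced to randomly recruit 6 eligible clusters within the intervention arm municipality, which has 10-15 villages", and the same is done on the control side.
- Random Allocation says what the random numbers are for: "A random number will be generated to recruit villages randomly within each arm". It also says that the two sets of villages lie far apart and under separate administrations.

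Statistical Methods plans a comparison of arms after 6 months using cluster summaries, with village as the random effect: "A random effects model will be applied to control possible confounders in individual and cluster levels". Challenges and Limitations admits that the approach may have limitations, but says that it "would minimize the residual confounders caused by differences in characteristics of the municipalities".

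**The concern.** Random selection and random allocation do different work. Drawing 6 villages at random from a subdistrict makes them representative of that subdistrict. It does nothing to make the two arms exchangeable. As described, a village's arm follows from where it lies, so the treatment contrast and the subdistrict contrast are one number.

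Any difference between the two subdistricts that bears on caregiver burden, such as municipal services, budgets or the existing level of burden, is therefore counted as an effect of the intervention. The village random effect describes variation among villages within a subdistrict. It cannot estimate a subdistrict effect that is collinear with arm. The planned tests and intervals treat 6 + 6 villages as the independent units and will be too narrow if subdistricts differ at all. The article addresses policymakers in Thailand and the region, so what the design can support matters.

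**Working it through.** **1. The plan's own sample size.** Inputs from Sample Size: difference 0.5, SD 4, alpha 0.05 (taken as two-sided), design effect 1.2, dropout 20%. Power is not stated; 90% is assumed.

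- n per arm = 2 × (1.960 + 1.282)² × 4² / 0.5² = 1345
- × 1.2 = 1614
- / (1 − 0.2) = 2018 per arm, 4036 in total, against the stated 4000

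The figure reproduces on that assumption. Its only allowance for clustering is the design effect of 1.2. With 300 to 350 people per village this implies an intracluster correlation of 0.2/299 = 0.00067 to 0.2/349 = 0.00057, or about 0.06-0.07%. There is no term for the subdistrict.

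**2. Counting assignment units.** Allocating 12 villages at random, 6 to each arm, gives C(12,6) = 924 possible allocations. Here the arm is fixed by subdistrict, leaving 1 + 1 area units and 2 − 2 = 0 degrees of freedom to separate subdistrict from treatment. Even if the two roles had been drawn by lot, there would be only 2 allocations, and a two-sided randomization test could give no P value below 2/2 = 1.

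**3. What subdistrict variation could do (illustration).** The document gives no between-subdistrict variance, so let r be an assumed share of the total variance. With no treatment effect and an unadjusted comparison:

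- SD of the subdistrict part of the arm difference: s = 4 × √(2r)
- chance that this part alone exceeds the target: P(|Z| > 0.5/s)
- standard error that a village-level analysis would use: SE = √(2 × 4² × 1.2 / n), which is 0.155 for n = 1600 per arm (after 20% dropout) and 0.139 for n = 2000
- true type I error of a nominal 5% test: the chance that a normal variable, or a t variable with 10 df, exceeds its critical value × SE/√(SE² + s²)

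| r (assumed) | s | P(exceeds 0.5) | True type I error (range over n and z or t) |
|---|---|---|---|
| 0.06% | 0.14 | 0.03% | 13-17% |
| 0.07% | 0.15 | 0.08% | 14-18% |
| 0.25% | 0.28 | 8% | 31-39% |
| 0.5% | 0.40 | 21% | 44-52% |
| 1% | 0.57 | 38% | 57-64% |

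The first two rows use the share implied by the plan's design effect. Recruiting more people or more villages in the same two subdistricts does not reduce s.

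**4. The confounding statement.** Taking all intervention villages from one municipality and all control villages from another places the whole municipality difference inside the arm contrast. That is the reverse of what Challenges and Limitations says.

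**The case against.** The design is not hidden. The article says openly that villages could not be assigned across municipalities, gives contamination as the reason for a cluster design, warns of baseline imbalance and asks for a baseline check. The subdistricts lie in the same district and are described as similar in population, ageing rate and access to health care. The Caregiver Burden Inventory (CBI) is measured at baseline in both arms, so a stable difference can be seen and adjusted for. The variance shares are assumed, and at the clustering the plan itself uses, a spurious difference as large as 0.5 is very unlikely.

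Much of this stands. It makes the design defensible as a pragmatic choice and keeps the magnitude illustrative. It does not make the label right or repair the confounding statement. Similarity is asserted, and a baseline check can reveal measured imbalance but cannot restore randomization. The design effect of 1.2 concerns villages and puts no bound on subdistrict variance.

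A reader might infer more than the document supports:

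- That the roles were deliberately chosen, or that no village could ever have had the other arm. The article does not say how the subdistricts got their roles; it only describes no random step.
- That the random numbers merely decide who is surveyed. In the intervention subdistrict the selected villages also receive the programme (Care Prevention Exercise Program; Results).
- That the two areas responded differently to COVID-19. Results reports the suspension and the emergency declaration, and no difference between areas.
- That 21% or 38% estimates the error in this trial. Neither does.

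**Conclusion.** The point holds as a contradiction within the protocol article and a wrong statement about confounding. What is described is a controlled comparison of two subdistricts, one per arm, with random selection of villages inside each. This follows from the text and needs no assumed figure. The planned intervals and P values leave out between-subdistrict variation, and the data cannot supply it.

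How far this distorts the result is unknown. Over assumed shares from 0.06% to 1%, in an unadjusted comparison, the chance that subdistrict variation alone exceeds the target runs from below 0.1% to 38%. The type I error is above 5% throughout, reaching 13-18% at the lowest shares shown. Baseline adjustment would shrink the part due to stable differences. It would not deal with trends that diverge during follow-up.

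**What to change.** 1. In the abstract, Trial Design and the randomization sections, describe the study as a non-randomized controlled comparison of two subdistricts with random selection of villages within each. State how the two subdistricts received their roles.
2. In Challenges and Limitations, delete or reverse the statement on confounding by municipality, and say that arm and subdistrict coincide.
3. State with the results that intervals and P values exclude between-subdistrict variance.
4. Use a baseline-adjusted or difference-in-differences contrast of CBI as the primary estimate, since Statistical Methods states only a comparison after 6 months. If the analysis plan already does this, nothing changes. If not, date and document the change, because Results reports the intervention as delivered and evaluation under way.
5. Limit the causal conclusion to these two subdistricts, and make it conditional on their having otherwise changed alike.

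The cost is rewording and possibly one documented change of analysis. No further participants or data are needed. The price is a less favourable design label and a weaker claim.
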